#### Inclusion criteria

The study is open to all the participants of the cardiac rehabilitation programme of the Skibotn Rehabilitation Centre that have access to Internet after their stay at Skibotn, have a personal mobile phone, are willing to participate and have signed the informed consent form.

#### Sample size estimation

Power analysis for *a priori* sample size estimation was performed with equivalence test for two-proportions in a cluster-randomized design by the computer program PASS [28]. The participants that attend the cardiac rehabilitation programme together a given month, consist a cluster. Based on previous research with chronic disease self-management [29] it is reasonable to expect that the proportions meeting goals for all self-management behaviours at one-year follow-up will be relatively low *e.g.*, 15% *vs.* 5%. To discover differences of this size between two groups at a 0.05 alpha level and with 0.80 power, we need a total sample of 16 clusters with 15 participants each. We will recruit a total of 17 clusters, equalling continuous recruitment of all the participants of the cardiac rehabilitation programme of Skibotn Centre over 18 months.

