### Control internet-based intervention

All participants will be given access to a basic Internet-based intervention, “ikkegideg.no” (Norwegian for “Don’t give up”), consisting of general information about CVD and self-management, including diet, physical activity, smoking and medication, and a discussion forum. In the discussion forum we have two levels of accessibility. There is the closed groups level, where the users are able to create and take part in discussions that are only accessible by those that are members in the same monthly group. Users that belong to the same monthly group have met physically during the rehabilitation programme and it is expected that the level of trust among them will be higher. At the same time, all the users will be able to create, read and take part in discussions that will be visible by all the registered users of the website. This helps the discussion forum to become more active, since more users will be contributing to the discussions.

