### Measures

For an overview of all measures over the different measurement time points, please see Table 1.

**Table 1 T1:** Overview of measures over the different time points of the study

	**Baseline**	**Post-rehab**	**1 month**	**3 months**	**12 months**
Socio-economic status	Y				
Co-morbidity	Y				Y
Alcohol use	Y				Y
Health-related Internet use	Y				Y
Disease related symptoms	Y	Y	Y	Y	Y
iPAQ	Y	Y	Y	Y	Y
Social support	Y	Y	Y	Y	Y
Self-efficacies	Y	Y	Y	Y	Y
HADS	Y	Y	Y	Y	Y
Perceived Tailoring			Y	Y	Y
Stage of change	Y	Y	Y	Y	Y
Decisional balance	Y	Y	Y	Y	Y
Regulatory focus	Y				
7-day smoking abstinence	Y	Y	Y	Y	Y
Quality of life	Y	Y	Y	Y	Y
Usage logging	Y	Y	Y	Y	Y
User evaluation			Y		Y
Return to work	Y		Y	Y	Y

The main outcome for this study is maintenance of physical activity, measured through self-report. Secondary outcomes are self-efficacy, perceived social support and user evaluation of the intervention. In order to link outcomes to use of the intervention we will assess perceived tailoring, and use of the intervention through web logging.

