### Statistical analysis

As participants are randomized at group level, a multilevel analysis will be performed to check for clustering effects. If the intraclass correlation coefficients for our primary outcome variables are different from zero this will be taken into account in the following analyses, in order to reduce p-value bias. Potential confounders will be added as covariates. Data analysis will be performed using IBM SPSS and MLWiN. Group differences after intervention will be analysed with baseline data as a covariate in ANCOVA. Should clustering effects be found, multilevel mixed regression will be used.

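### The stated 80% power is for a comparison of goal-attainment proportions, not for the planned baseline-adjusted analysis of self-reported physical activity

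*Protocol article*

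**What the plan says.** **Sizing.** Under Sample size estimation, the method is an "equivalence test for two-proportions in a cluster-randomized design". The quantity is a proportion at one year: "the proportions meeting goals for all self-management behaviours at one-year follow-up will be relatively low", with 15% against 5% as the example. The error rates are set "at a 0.05 alpha level and with 0.80 power", and the result is that "we need a total sample of 16 clusters with 15 participants each". The same section adds: "We will recruit a total of 17 clusters".

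**Main outcome.** Under Measures: "The main outcome for this study is maintenance of physical activity, measured through self-report". The Abstract (Methods/Design) words it as the level of physical activity and names one month, three months and one year. The instrument is IPAQ. The secondary outcomes are self-efficacy, perceived social support and user evaluation.

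**Analysis.** Under Statistical analysis: "Group differences after intervention will be analysed with baseline data as a covariate in ANCOVA". If clustering effects are found, multilevel mixed regression is used. No comparison of proportions is described.

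**The concern.** A power statement carries meaning only for the endpoint, test and time point it was computed for. Here the sizing and the primary analysis differ on all three: a goal met or not met against an activity level, a two-proportions test against ANCOVA or a mixed model, and one year alone against three follow-up times.

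What is at stake is how the result can be read. If the trial finds no difference in activity, a reader will want to know whether an effect worth having has been excluded. The 80% figure cannot answer that, and the article gives no IPAQ difference, SD, ICC or baseline correlation from which to work it out. The mismatch does not bias the treatment estimate or change the type I error.

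**Working it through.** **1. Endpoints side by side**

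| | Sample size estimation | Abstract, Measures, Statistical analysis |
|---|---|---|
| Endpoint | Proportion meeting goals, all self-management behaviours | Level or maintenance of physical activity (IPAQ) |
| Scale and test | Binary; two proportions | Baseline-adjusted ANCOVA, or multilevel mixed regression |
| Time | One year | 1, 3 and 12 months |

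The goal proportion is neither the main outcome nor one of the secondary outcomes, and no threshold for an activity goal is given. The control website is described as "including diet, physical activity, smoking and medication, and a discussion forum". Of those behaviours, the article names measures only for physical activity (IPAQ) and smoking (7-day abstinence).

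**2. The plan's own figure**

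Inputs from the article: p1 = 0.15, p2 = 0.05, alpha 0.05, power 0.80, 16 × 15 = 240, taken here as 120 per arm. Not given: sidedness, ICC, equivalence margin.

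For a difference test without continuity correction, with mean proportion 0.10:

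n per arm = [z_α √(2 × 0.10 × 0.90) + z_β √(0.15 × 0.85 + 0.05 × 0.95)]² / 0.10²

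- Two-sided (1.960, 0.842): 141 per arm, 282 in total before clustering, or at least 10 clusters of 15 per arm. This does not give 240. Power at 120 per arm is 73.6% at ICC 0.
- One-sided (1.645, 0.842): 111 per arm, which rounds up to 8 clusters per arm, 16 in all. Power is 82.9% at ICC 0, 80.6% at 0.005 and 78.4% at 0.01.

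The cluster count is therefore recovered only with an unstated one-sided test and an ICC close to zero. An equivalence version cannot be checked without a margin. The inputs are too incomplete to call the figure right or wrong. Under every variant the power refers to two proportions.

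**3. What 16 clusters of 15 would detect on a continuous activity measure**

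Assumptions, because the article gives none: ICC 0, 0.02 or 0.05; baseline correlation r = 0 or 0.5; no attrition; two-sided 0.05; 80% power.

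- Degrees of freedom: 16 clusters − 2 = 14, critical t = 2.145. The noncentrality that gives 80% power is 3.013.
- Effective n per arm = 120 / (1 + 14 × ICC).
- Detectable standardised difference = 3.013 × √(2 / effective n) × √(1 − r²). The last factor assumes that adjustment reduces the variance by the same share between and within clusters. For r = 0.5 it is √0.75 = 0.866.

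| ICC | Design effect | Effective n per arm | r = 0 | r = 0.5 |
|---|---|---|---|---|
| 0 | 1.00 | 120.0 | 0.39 SD | 0.34 SD |
| 0.02 | 1.28 | 93.8 | 0.44 SD | 0.38 SD |
| 0.05 | 1.70 | 70.6 | 0.51 SD | 0.44 SD |

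A normal approximation (2.802 in place of 3.013) gives 0.36, 0.41 and 0.47 SD for r = 0, slightly optimistic with only 16 clusters. On that approximation, with r = 0, a true difference of 0.3 SD would have power of 64%, 54% and 43% at the three ICCs.

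**The case against.** **The word all may mean each.** The sizing sentence can be read as the proportion for each behaviour separately, which would include physical activity, and maintenance of activity can be expressed as met or not met. That reading is fair and narrows the gap. It does not close it: the sizing would then be for a dichotomised activity goal that the article neither defines nor analyses.

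**A reader might infer that the composite cannot be formed because diet and medication are not measured.** The article does not establish this. It never lists the behaviours in the composite, and the website topics describe information content. Table 1 is an overview and is not complete: the eHealth Literacy Scale appears in the text under Measures without a row of its own. All that can be said is that the article names no diet or medication measure.

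**A reader might infer that 15% against 5% has no bearing on activity.** That depends on what the cited chronic disease study reported, which cannot be seen here.

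**A reader might infer that the trial is underpowered.** The article gives no target difference, SD, ICC or baseline correlation for IPAQ, so this cannot be determined. The detectable differences above move with the assumptions chosen.

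**An article condenses a fuller protocol.** That would excuse an omission. Here the sizing basis, the main outcome and the analysis are all stated, and they do not match.

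**Conclusion.** The point holds. The 0.80 power is attached to a comparison of proportions that is not a listed outcome and has no described analysis, so it does not apply to the primary analysis of physical activity. The mismatch can be read off the text and needs no assumption.

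Its size can only be illustrated: detectable differences of 0.34 to 0.51 SD over ICC 0 to 0.05 and baseline correlation 0 or 0.5, for 8 against 8 full clusters without attrition. Whether that range is adequate cannot be judged from the article. This should be fixed, but it does not put the trial's validity at risk: the gap is in the justification and in how a null result can be read.

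**What to change.** Under Sample size estimation:

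1. Keep the 15% against 5% calculation as the historical, a priori basis for 16 clusters of 15. Recruitment is already open, and deleting it would misreport how the size was chosen.
2. State that its power does not apply to the main outcome.
3. Add, labelled as a later calculation, the standardised difference in IPAQ activity that the baseline-adjusted analysis can detect allowing for clustering. Give the ICC and baseline correlation as assumptions, with a range.
4. Make that calculation for the time point the sponsor designates as primary. The article names three and selects none.

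The values in the table above show the form of the statement; they are not figures to adopt, since they rest on assumed inputs. The cost is text and a short calculation. Enrolment and data collection do not change.

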### Aims and hypotheses

Our aim is to assess the effects of a tailored Internet- and mobile-based intervention on maintenance of self-management behaviours after a cardiac rehabilitation stay. Our hypothesis is that the intervention group (tailored) will have higher adherence to the Internet-based intervention, and be more physically active.

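### The sample size is tied to an equivalence test although the trial asks a superiority question; two-sided at 0.05, 16 clusters of 15 give about 74% power before any clustering

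*Protocol article*

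**What the plan says.** In the Protocol article, Sample size estimation, the power analysis is described as an "equivalence test for two-proportions in a cluster-randomized design". The expected proportions meeting self-management goals at one year are given, as an example, as 15% and 5%. The target of the calculation is put this way: "To discover differences of this size between two groups at a 0.05 alpha level and with 0.80 power". The size it arrives at follows: "we need a total sample of 16 clusters with 15 participants each". The section then sets the recruitment goal slightly higher: "We will recruit a total of 17 clusters".

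Aims and hypotheses predicts that "the intervention group (tailored) will have higher adherence to the Internet-based intervention, and be more physically active". Statistical analysis plans to compare the groups after the intervention by ANCOVA with baseline as covariate, or by a multilevel model if clustering is found.

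The error rate is given only as "at a 0.05 alpha level". The section states no sidedness, ICC, equivalence margin or allocation ratio.

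**The concern.** Power in an equivalence test is the probability of showing that two arms do not differ by more than a margin. It is not the probability of detecting a difference of 15% against 5%. The hypothesis, the stated purpose of the calculation and the planned analysis are all about a difference, so the named test contradicts the rest of the article.

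What is at stake is how the result is read. A null finding would be taken as coming from a trial with 80% power to see the planned effect. If the test is two-sided, as is usual, the real figure is lower, and it falls quickly once participants in the same monthly group resemble each other.

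**Working it through.** **Inputs from the Protocol article (Sample size estimation).** Proportions p1 = 0.15 and p2 = 0.05; alpha 0.05; power 0.80; 16 clusters × 15 = 240 participants.

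**Assumptions, because no figure is given.** Allocation 1:1, so 8 clusters or 120 participants per arm. ICC from 0 to 0.05. Both one-sided and two-sided tests are tried. No attrition.

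**Formulas.** Difference d = 0.10; mean proportion 0.10.
- Participants per arm, pooled variance: n = [z_alpha·√(2·0.10·0.90) + z_power·√(0.15·0.85 + 0.05·0.95)]² / d² = [z_alpha·√0.18 + 0.842·√0.175]² / 0.01.
- Design effect for clusters of 15: DE = 1 + 14·ICC; effective n per arm = 120/DE.
- Power = Φ{[0.10 − z_alpha·√(0.18/n)] / √(0.175/n)}.

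**Step 1: can the plan's 16 clusters be reproduced?**
- One-sided 0.05 (z = 1.645), ICC 0: n = 110.2, so 111 per arm; 111/15 = 7.4, rounded up to 8 clusters per arm, or 16 in total. This matches.
- Two-sided 0.05 (z = 1.960), ICC 0: n = 140.1, so 141 per arm; 141/15 = 9.4, rounded up to 10 clusters per arm, or 20 in total. This does not match.
- Equivalence by two one-sided 0.05 tests, with an assumed margin of 10 points and a true difference of 0: power is 0.944 at a common rate of 5% and ICC 0, falling to 0.80 at an ICC of about 0.034; at a common rate of 10% and ICC 0 it is 0.651. So 0.80 can be reached this way too, but it is power to show equivalence.

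**Step 2: superiority power with 16 clusters.** At ICC 0 and n = 120, √(0.18/120) = 0.03873 and √(0.175/120) = 0.03819.
- Two-sided: (0.10 − 1.960·0.03873)/0.03819 = 0.631; Φ = 0.736.
- One-sided: (0.10 − 1.645·0.03873)/0.03819 = 0.950; Φ = 0.829.

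| Assumed ICC | DE | Effective n per arm | Two-sided | Two-sided, t on 14 df | One-sided |
|---|---|---|---|---|---|
| 0 | 1.00 | 120.0 | 0.736 | 0.683 | 0.829 |
| 0.01 | 1.14 | 105.3 | 0.679 | 0.626 | 0.784 |
| 0.02 | 1.28 | 93.8 | 0.628 | 0.577 | 0.741 |
| 0.05 | 1.70 | 70.6 | 0.508 | 0.464 | 0.633 |

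The t column uses the noncentral t with unpooled variance on 16 − 2 = 14 degrees of freedom. One-sided power is exactly 0.80 at an ICC of about 0.006 (0.008 with unpooled variance).

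**Step 3: does the choice of two-sided formula matter?** At 120 per arm and ICC 0: unpooled 0.745, arcsine 0.760, exact enumeration of the pooled z test 0.763 and of the unpooled z test 0.766, Fisher exact 0.674. All are below 0.80.

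**Step 4: all 17 clusters (9 against 8, or 135 against 120).** Two-sided at ICC 0: 0.755 to 0.780, depending on which arm has the extra cluster and on pooled or unpooled variance.

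**Step 5: difference detectable with 80% power, two-sided, 16 clusters.** Against 5%: 16.0% at ICC 0, 18.0% at ICC 0.02 and 20.6% at ICC 0.05.

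**The case against.** The strongest reply is that the article never says the test is two-sided. Its hypothesis is directional, and a one-sided 0.05 superiority calculation gives exactly 16 clusters. This stands. It rules out two stronger statements that a reader might infer: that the design flatly lacks 80% power, and that no superiority calculation yields 240. It does not make the stated figure safe. The one-sided test is undeclared, and 80% then holds only up to an ICC of about 0.006 with 16 clusters. That is very little room in a trial that randomises groups living together for four weeks.

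Second, the word equivalence may be a slip: two different rates are given and no margin. That is possible, and the article cannot show which calculation was run. Either way the named method is wrong for the question and needs correcting.

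Third, a condensed article may leave the ICC and the margin to a fuller document. This also stands, so their absence is not the fault raised here. The fault is the named test, which contradicts the hypothesis within the same article. It also means that every power figure at an ICC above 0 is conditional on an assumed value.

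Fourth, the rates are examples for self-management goals, whereas the planned analysis is baseline-adjusted ANCOVA or a multilevel model of self-reported activity. The figures here therefore test the plan's own calculation; they are not the power of the final model.

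A reader might also suspect that 16 clusters per arm was reported as a total, because 141 × 1.7 / 15 = 15.98 at an ICC of 0.05. That ICC is assumed, the text says total, and nothing in the article supports the inference.

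**Conclusion.** The point holds in this form: the sample size names an equivalence test for a superiority question, so the stated 0.80 is tied to the wrong test.

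Read as a two-sided 0.05 superiority test, 16 clusters of 15 fall about 6 percentage points short with no clustering (74%), and further short with it (51% at ICC 0.05). The 17th cluster brings power to 76–78% at ICC 0. Read as one-sided, the stated number is reproduced, but 80% is lost once the ICC passes about 0.006; power is then 74% at 0.02 and 63% at 0.05.

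The contradiction over the test needs no assumption. The sizes rest on 1:1 allocation, 15 analysed participants in every cluster, no attrition and the ICC values shown.

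**What to change.** In Sample size estimation, replace the equivalence calculation with a superiority calculation for two proportions in a cluster-randomised design, and declare the sidedness and the assumed ICC. Then do one of the following, without adding clusters:

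- restate the power for 16 to 17 clusters of 15 over an ICC range of 0 to 0.05, which two-sided is about 51–78% by the z-approximation and lower with a t reference on 14 degrees of freedom; or
- keep 80% power and restate the two-sided detectable difference for 16 clusters as about 5% against 16–21%.

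The cost is one rewritten paragraph and a less favourable stated power. Recruitment and conduct do not change.

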## Design

Skibotn Rehabilitation Centre receives each month (except from July) a group of 10–20 CVD patients that are admitted in the rehabilitation programme. Since these people are hosted in the same environment for all of this period and social interaction related to the rehabilitation is encouraged, a randomisation among the members of the same group would make it very likely for patients to realize whether they belong to the control or intervention branch. In order to minimize this risk of contamination of the control group, the participants will be blinded to condition by randomizing the monthly clusters of participants to one of two conditions:

(1) A control condition involving a basic Internet-based self-management intervention

(2) An experimental condition where the participants get access to a tailored and enhanced version of the Internet-based intervention

The researchers are also blinded for the condition of each monthly group, so we will avoid introducing any bias in the analysis of the data. To ensure true randomness of the groups, we used random.org to allocate the groups to the two conditions. Random.org is a true random number online service that is based on the atmospheric noise. The duration of the study is one year after the discharge from the cardiac rehabilitation programme.

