### Methodological considerations

Many of the methodological considerations of this study are related to its online nature. First of all, the population that we target, individuals with CVD history, is not in a large extent –because of their age– familiar with the Internet and the mobile technology. That makes recruitment challenging and it might introduce a bias related to the socioeconomic status of those that have access to the Internet and can take part in the study. In the same age group, we expect that women are even less familiar with new technologies and this might lead to underrepresentation of women in the sample.

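### Fifteen participants per cluster is the midpoint of the centre's whole monthly intake, so 17 clusters yield 240 one-year outcomes only if about 94% of admitted patients enrol and answer

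*Protocol article*

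**What the plan says.** The protocol article's Sample size estimation section states "we need a total sample of 16 clusters with 15 participants each". This is meant to detect proportions meeting self-management goals at one year that "will be relatively low *e.g.*, 15% *vs.* 5" per cent, "at a 0.05 alpha level and with 0.80 power". It then plans 17 clusters, "equalling continuous recruitment of all the participants of the cardiac rehabilitation programme of Skibotn Centre over 18 months".

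The Design section says that the centre receives, every month except July, "a group of 10–20 CVD patients that are admitted in the rehabilitation programme". That is the whole intake, before any selection for the trial.

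The Inclusion criteria admit only those who "have access to Internet after their stay at Skibotn, have a personal mobile phone, are willing to participate" and have signed consent. Ethical aspects calls the sample a convenience sample of volunteers. Methodological considerations says that the target population is largely unfamiliar with the Internet and mobile technology, and adds: "That makes recruitment challenging". Under Procedure, follow-up is by questionnaire, prompted by email and SMS, at 1, 3 and 12 months.

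**The concern.** The power calculation needs participants who contribute a one-year outcome. The paragraph obtains its clusters by counting everyone who attends the programme. Three filters lie between those two counts: eligibility (Internet and phone), consent, and response at 12 months. The article describes all three and itself expects recruitment to be difficult, but the stated size leaves room for them only through one spare cluster.

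At stake is how the result is read. If the analysed sample is well below 240, a null result would be set against a stated 80% power that the described design probably did not have.

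**Working it through.** **Inputs.** From Sample size estimation: 15% vs 5%, alpha 0.05, power 0.80, 16 clusters of 15 required, 17 planned. From Design: 10 to 20 admitted per month. Assumed here because the document does not give them: mean intake 15 (the midpoint), a two-sided test, the intracluster correlation (ICC), and the enrolment and response rates.

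**The plan's own figure.** 16 × 15 = 240, or 120 per arm. The unpooled formula, two-sided and with no clustering, needs per arm (1.960 + 0.842)² × (0.15 × 0.85 + 0.05 × 0.95) / 0.10² = 137.4, which is 275 in total. On that basis 240 gives 74% power. One-sided it needs 217 in total, and 240 is recovered with an unstated ICC of about 0.008 (about 0.006 with the pooled formula). The stated inputs alone therefore do not reproduce 240. That is a separate matter, but it means that power below must be compared with a no-loss row and not with 80%.

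**Calendar.** Eighteen months without July contain 16 or 17 monthly groups, depending on the start month, so 17 clusters is consistent.

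**Supply.** Required combined yield = 240 / (17 × monthly intake), where yield = eligible × consenting × answering at 12 months.

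| Patients per group | Admitted in 17 groups | Yield needed for 240 |
|---|---|---|
| 10 | 170 | 141% (impossible) |
| 15 (midpoint) | 255 | 94.1% |
| 20 | 340 | 70.6% |

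At the midpoint the reserve is 255 − 240 = 15 patients, or 5.9%, to cover all three filters together.

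**Power with 17 clusters.** Let m = 15 × enrolled × answering, with nine clusters in the 15% arm and eight in the 5% arm. The variance of the difference is [1 + (m − 1) × ICC] × [0.1275 / (9m) + 0.0475 / (8m)]. Power is taken from the normal distribution and from a noncentral t on 15 degrees of freedom (z / t).

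Example with no loss and ICC 0: 0.1275/135 + 0.0475/120 = 0.001340, standard error 0.0366, 0.10/0.0366 = 2.73, and 2.73 − 1.96 = 0.77, which gives 78%.

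| Enrolled × answering (assumed) | Analysed | ICC 0 | ICC 0.05 (assumed) |
|---|---|---|---|
| No loss | 255 | 78% / 72% | 55% / 50% |
| 80% × 80% | 163 | 59% / 53% | 45% / 40% |
| 70% × 70% | 125 | 48% / 43% | 38% / 34% |

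With eight clusters in the 15% arm, the figures are about two points lower. The loss from 255 to 163 costs about 19 points at ICC 0 and about 10 at ICC 0.05. At the higher ICC much of the distance from 80% comes from clustering and not from recruitment.

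**More generous cases.** One-sided at ICC 0 (z), 80% × 80% gives 71% and 70% × 70% gives 61%. With 20 admitted every month, 80% × 80% leaves 218 analysed and two-sided power of 71% (z, ICC 0).

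**The case against.** Four points can be made for the plan.

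- **A 17th cluster is planned.** A reader might infer that every admitted patient must be eligible, consent and respond. That is true only of the 16 required clusters. With the 17th the figure at the midpoint is 94%. This stands, though a margin of 6% is thin.
- **No mean intake is stated.** A reader might also infer that 240 cannot come from 17 monthly groups. The document does not support that. With 20 patients in every group, a combined yield of 71% suffices, and no uptake or response rate is given to rule it out. Unlikely at the midpoint is as far as the text goes.
- **The article does not promise 15 analysed participants per cluster.** It says that 15 are needed and, separately, that 17 clusters will be recruited. This stands. The fault lies in equating those clusters with everyone in the programme.
- **A condensed article may leave uptake and attrition rates to the full protocol.** This also stands, and their absence alone would be no finding. But the article itself states the size, the source and the recruitment window, and these fit poorly with its own account of who can enter.

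It is also fair to say that the power figures rest on a two-sided test and, in one column, on an ICC that the article does not state. That is why the no-loss row is needed.

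**Conclusion.** The point holds in this form: the stated cluster size sits at the midpoint of the unselected intake, and the one-cluster reserve does not make 240 one-year outcomes likely under the article's own description of recruitment and follow-up. Treating 17 clusters as the whole programme population therefore does not support the stated 80% power.

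The required combined yield is about 94% at 15 per month, 71% at 20, and unattainable at 10. Attributable to loss alone, power falls from 78% / 72% to 59% / 53% under assumed 80% enrolment and 80% response (two-sided, ICC 0). These rates are illustrations, and the midpoint intake is an assumption. The direction of the conclusion does not depend on the exact rates, but the size does.

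**What to change.** In Sample size estimation, replace the statement that 17 clusters equal recruitment of everyone in the programme with two numbers per cluster: expected enrolled, and expected analysed at 12 months. Take them from uptake and response seen so far where available, and otherwise give them as stated assumptions. The article says that recruitment is open but reports no such figures.

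Then restate the power, or the detectable difference, for 17 clusters at the analysed cluster size, naming the sidedness and ICC used.

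The cost is one rewritten paragraph and probably a less favourable power figure. No added enrolment is needed.
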